## Abstract

**Background:**

Older adults with multiple chronic illnesses are at risk for worsening functional and medical status and hospitalization. Home telemonitoring may help slow this decline. This protocol of a randomized controlled trial was designed to help determine the impact of home telemonitoring on hospitalization. The specific aim of the study reads as follows: to determine the effectiveness of home telemonitoring compared with usual care in reducing the combined outcomes of hospitalization and emergency department visits in an at-risk population 60 years of age or older.

**Methods/Design:**

Two-hundred patients with the highest 10% Mayo Clinic Elder Risk Assessment scores will be randomly assigned to one of two interventions. Home telemonitoring involves the use of a computer device, the Intel Health Guide, which records biometric and symptom data from patients in their homes. This information is monitored by midlevel providers associated with a primary care medical practice. Under the usual care scenario, patients make appointments with their providers as problems arise and use ongoing support such as a 24-hour nurse line.

Patients will have initial evaluations of gait and quality of life using instruments such as the SF-12 Health Survey, the Kokmen Short Test of Mental Status, and the PHQ-9 health questionnaire. Patients will be followed for 1 year for primary outcomes of hospitalizations and emergency department visits. Secondary analysis will include quality of life, compliance with the device, and attitudes about telemonitoring. Sample size is based on an 80% power to detect a 36% difference between the two groups. The primary analysis will involve Cox proportional time-to-event analysis. Secondary analysis will use t-test comparisons for continuous variables and the chi square test for proportional analysis.

**Discussion:**

Patients randomized to home telemonitoring will have daily assessments of their health status using the device. Registered nurse monitoring will assess any change in status followed by videoconferencing by a mid-level provider. We obtained trial registration and Institutional Review Board approval.

**Trial registration:**

Trial registration number through http://www.clinicaltrials.gov: NCT01056640.

## Background

Older adults with multiple chronic conditions endure functional decline and loses independence. An estimated two thirds of deaths in the older population are due to chronic diseases. Five percent of patients are responsible for 50% of the costs in most healthcare systems[1]. Yet the healthcare system often places the burden of accessing healthcare on the individual patient. While this task may be easy for healthy younger adults, the older, frail population encounters numerous obstacles, including difficulty recognizing important changes in status. In response, healthcare systems have attempted to preemptively evaluate at-risk patients prior to functional decline. These methods have included more frequent prescheduled outpatient physician visits, home phone calls from the physician office, home healthcare, and home visits by physicians or midlevel providers. While each of these methods has its advantages, they are labor- and time-intensive processes that may exacerbate the healthcare worker shortage^2^. They also may miss the mark in caring for at-risk patients. Clearly, we need a more timely system of providing optimal care to chronically ill patients. Home telemonitoring, the use of audio, video, and other telecommunication technologies to monitor patient status at a distance, has emerged as a viable method for caring for this population.

Home telemonitoring may reduce hospital admissions, emergency department (ED) visits, and hospital length of stay[2]. A systematic review suggests a 20% reduction in hospitalization in home telemonitoring groups compared with the usual care in patients with cardiovascular disease[3]. However, it remains unclear if home telemonitoring will reduce hospitalizations and ED visits in older patients with multiple medical problems. We propose to answer this question in a sample of high-risk adults at least 60 years of age with mixed chronic diseases in a randomized controlled trial. Our primary aim is to evaluate the effectiveness of home telemonitoring for reducing hospitalizations, emergency department visits, and the composite outcomes of hospitalizations and ED visits compared with usual care. Our secondary aims are to evaluate the effectiveness of home telemonitoring for improving functional status, quality of life, patient attitudes, behaviors, compliance, mood, and cognitive status compared with usual care. Furthermore, we intend to evaluate the effectiveness of home telemonitoring for decreasing total healthcare costs, 30-day re-hospitalization rates, and hospital bed days.

## Methods/Design

### Study design

This multi-site, randomized controlled trial of home telemonitoring or usual care will take place in the four sites of the outpatient practice of Mayo Clinic's Division of Primary Care Internal Medicine (PCIM) in the Department of Family Medicine (FM) in Rochester, Minn. and nearby Kasson, Minn. The Mayo Elder Risk Assessment (ERA) Index will be used to randomly assign 200 high-risk patients to home telemonitoring or usual care (100 patients per intervention). Patients will be followed for 1 year after enrollment. Patients in the Rochester practice will be block-randomized as a single entity, and the patients in the Kasson practice will be block-randomized as a second entity. Subjects and providers will not be blinded to the allocation of the intervention, but analysis will be blinded to the allocation type.

### Human Subjects approval and Informed Consent

We obtained institutional review board approval from the Mayo Clinic Institutional Review Board (IRB) on Oct. 30, 2009. All patients provided written informed consent prior to enrollment and randomization. All written communication and the informed consent and protocol were reviewed by the IRB.

### Patient populations

The identification of high-risk older adults in the PCIM practice has centered on the development of the ERA, which uses the Mayo Clinic administrative databases and the Generic Disease Management System (GDMS) to electronically identify high-risk older adults who live in an assisted-living setting. Each patient older than 60 years in the PCIM and FM panel receives a score and quartile placement. The specific scoring for the ERA is detailed in Table 1. Patients with an ERA score greater than 16 will be included in the study.

**Table 1 T1:** Scoring system of the Mayo Clinic Elder Risk Assessment

Married	-1
Age 70-79	1

Age 80-89	3

Age 90 or older	7

Race - Black	6

Race - Other	0

Race - Unknown	-6

1-5 hospital days in previous 2 years;	5

6 or more hospital days in previous 2 years	11

History of diabetes	2

History of CAD/MI/CHF	3

History of stroke	2

History of COPD	5

CAD, coronary artery disease; CHF, congestive heart failure; COPD, chronic obstructive pulmonary disease; MI, myocardial infarction.

### Exclusion criteria

Patients who live in a nursing home, have a clinical diagnosis of dementia, have a score of 29 or higher on the Kokmen Short Test of Mental Status, cannot give informed consent, or do not have the ability to use the Intel Health Guide (due to severe visual impairment and lack of a caregiver, an unwillingness to use the device, or lack of a grounded outlet or 3G mobile communications coverage) are excluded from the study.

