### Demographic and practice information

Most residents of Olmsted County who are age 60 or older are female and white (>90%)[4]. While county residents are largely Northern European, the ERA index places this ethnicity as a high-risk population; thus, the potential sample may slightly over represent underserved minorities as a high-risk group.

The PCIM and FM have a combined population of about 21, 000 patients in this age group. The selection criteria of a score of 16 or greater on the ERA places these individuals in the upper decile of risk for hospitalizations, ED visits, nursing home placement, and death. The ERA is an electronically derived index number provided to all patients in the in PCIM and FM via the GDMS (Table 1).

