#### Assessments

All patients enrolled in the study will participate in three face-to-face visits and two phone calls. The initial visit, 6-month visit, and 12-month visit will use instruments to measure functional status, quality of life, cognition, mood, self-reported outcomes, attitudes, behaviors, and compliance. At the initial visit, the patient's Mayo current visit information and family history will be collected. At 3 months and 9 months, the study team will call the patient for descriptions of quality of life and mood. If the results indicate a risk to the patient, the patient's primary care physician will be contacted. Specifically, if the patient health questionnaire PHQ-9 indicates depression (score >14)[5], or the Kokmen Short Test of Mental Status indicates memory loss or changes of functional status (≤29)[6], this finding will be reported to the primary care physician.

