The instruments used in this study measure quality of life, mood, functional status, activities of daily living, caregiver burden, and self-reported outcomes of hospitalization and ED visits. The SF-12, the short form of the SF-36, which measures quality of life and psychosocial factors[7], will determine if the quality of life has changed due to the intervention. The PHQ-9 is a validated instrument that measures depression using Diagnostic and Statistical Manual (DSM) 4 criteria for depression[5] and a scoring mechanism that can measure depressive symptoms over time. The Kokmen Short Test of Mental Status screens for cognitive decline using a 38-point screening instrument[6]. The functional measures include grip strength with tonometry, which can directly measure a person's strength in the upper extremities[8]. Both upper extremities will be tested and the best result used as the primary measure. The timed up-and-go test is a validated instrument that measures the ability to rise from a chair, turn, and return to the chair[9]. Lastly, gait speed is measured in meters per second. The patient is told to walk as quickly as possible for 6 meters. Standards for gait speed are established for older adults[10]. The Barthel Index is a self-reported questionnaire that evaluates activities of daily living for the subject[11]. The Caregiver Quality of Life Scale is used as the standard instrument for measuring caregiver stress and feelings. Outcomes include hospital admissions and visits to the ED within the past 3 months. The healthcare providers are surveyed once in the pre-stages of the study and once after completion. Providers are asked these questions:

• How confident are you in the home monitoring of your sickest patient?

• Do you feel that our practice has a good system of maintaining the functional status and health of our patients?

• How confident are you that a home-based system that allows monitoring of vital signs and symptoms will help in patient care?

• Would you be willing to recommend a home-based telemonitoring system that allows videoconferencing?

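### The Kokmen exclusion as printed runs against the protocol's own memory-loss cut-off: it admits only flagged scores and excludes every unflagged one

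*Protocol article*

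**What the plan says.** **Kokmen test.** In the protocol article, Exclusion criteria, patients are excluded if they "have a score of 29 or higher on the Kokmen Short Test of Mental Status". The same sentence separately excludes those who "have a clinical diagnosis of dementia", those who "cannot give informed consent", nursing-home residents, and those unable to use the telemonitoring device.

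The Assessments section uses the same test as a safety flag. The primary care physician is told if "the Kokmen Short Test of Mental Status indicates memory loss or changes of functional status (≤29"). That section also says the test "screens for cognitive decline using a 38-point screening instrument". Under Data analysis and in Table 4, the Kokmen score is a secondary outcome, compared between arms by t-test.

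**ERA index.** Patient populations states: "Patients with an ERA score greater than 16 will be included in the study". Demographic and practice information describes the rule differently, as "The selection criteria of a score of 16 or greater on the ERA", and says that this places patients in the top decile of risk.

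**The concern.** The Assessments section makes low Kokmen scores the worrying ones. An exclusion that removes high scores therefore points the wrong way. It turns away the patients about whom the protocol has no cognitive concern and keeps those about whom it does.

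An exclusion criterion fixes who is randomised and to whom the result applies. The stated aims concern high-risk older adults with mixed chronic disease, not a group selected for a low cognitive screen. If the printed rule was used:

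- the result would generalise only to patients already flagged on this test;
- the physician report would be triggered for everyone at the initial visit, so meeting the flag later could not mark new decline;
- the Kokmen secondary outcome would start with no unflagged patient in either arm.

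The ERA point is of the same kind but small. Two statements of one entry threshold differ for patients scoring exactly 16.

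**Working it through.** No power or sample-size formula applies. The check compares sets of scores.

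**Kokmen inputs**

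- Scale: whole-number scores 0 to 38, which is 39 values. The maximum of 38 is from Assessments; the minimum of 0 and whole-number scoring are assumptions.
- Excluded: score ≥ 29 (Exclusion criteria).
- Flagged: score ≤ 29 (Assessments).

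**Printed rule against the flag**

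| Scores | Number of values | Entry under Exclusion criteria | Flag under Assessments |
|---|---|---|---|
| 0–28 | 29 | admitted | flagged |
| 29 | 1 | excluded | flagged |
| 30–38 | 9 | excluded | not flagged |

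The values sum to 29 + 1 + 9 = 39. Of the 29 admitted values, 29 are flagged. Of the 9 unflagged values, none is admitted. A higher assumed minimum score would shorten the first row but change neither statement.

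**If only the direction is turned round**

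- Excluding scores below 29 admits 29 to 38; a patient at exactly 29 enters already flagged.
- Excluding scores of 29 or lower admits 30 to 38; nobody enters flagged.

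Reversing the direction therefore does not by itself settle how a score of 29 is treated.

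**Can an ERA score of exactly 16 occur?** All items in Table 1 carry whole points. A married patient (−1) aged 70–79 (1), with 6 or more hospital days in the previous 2 years (11) and COPD (5), scores −1 + 1 + 11 + 5 = 16. A married patient (−1) aged 80–89 (3), with 6 or more hospital days (11) and CAD/MI/CHF (3), also scores −1 + 3 + 11 + 3 = 16.

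Listing all item patterns gives 2 × 4 × 3 × 3 × 2 × 2 × 2 × 2 = 1,152 combinations, of which 55 total exactly 16. These are patterns, not patients, and the article gives no patient count at 16. Such patients are eligible under one section and ineligible under the other.

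**The case against.** The case on the other side is that this is a journal article, not the full protocol reviewed by the ethics board. The wording may be a slip that never reached the screening form. The article does not show the form, so it cannot settle this. That stands, and it makes every statement about who was enrolled conditional. It does not remove the contradiction, which no other section corrects.

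Four stronger readings are tempting, and the document does not support them:

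- **That the rule enrols people who cannot consent or cannot work the device.** Both groups are excluded separately in the same sentence, and Human Subjects approval and Informed Consent reports written consent from all patients. Read literally, the population is patients at 28 or below with no dementia diagnosis who can consent and can use the device. The exclusions are cumulative. The neighbouring ones indicate intent; they do not logically contradict the Kokmen clause.
- **That admitted patients are cognitively impaired and excluded patients cognitively normal.** The article presents the test as a screen with a reporting trigger. Flagged and unflagged is as far as it goes.
- **That the trial comparison is biased or its power figures wrong.** Eligibility is applied before allocation and equally to both arms, and no input in the Sample size section refers to the Kokmen score.
- **That only the 16-or-more ERA threshold fits the abstract's highest 10%.** If everyone at 16 or more is in the top decile, so is everyone above 16. The stricter rule is not shown to conflict with the abstract.

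**Conclusion.** The point holds for the text. As printed, the Kokmen exclusion admits only scores the protocol flags and excludes every score it does not. This rests on the two stated cut-offs and on whole-number scoring up to 38.

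That the direction in Exclusion criteria is the error is a strong inference, drawn from the low-score flag and the neighbouring exclusions, but not a certainty. If the printed rule was the one applied, all enrolled patients would score 28 or lower at entry, and the population, generalisability and Kokmen outcome would be restricted accordingly. If it was not, the fault is confined to the published wording. Either way an eligibility criterion is wrong as written and must be corrected.

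The ERA discrepancy is real but minor. It touches only patients at exactly 16, whose number is not given, and would not by itself warrant the same priority.

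**What to change.** 1. Reconcile Exclusion criteria with Assessments and correct the direction of the Kokmen exclusion.
2. State explicitly whether a score of exactly 29 is eligible, since that score is also flagged.
3. Confirm from the screening form which Kokmen rule was applied. Consent is reported in the past tense, so screening may already have begun. If the printed rule was used, describe the trial population and the Kokmen outcome accordingly.
4. As a side item, give one ERA threshold in both Patient populations and Demographic and practice information, and confirm which was applied to patients scoring exactly 16.

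The cost is a text correction or short amendment and a check of screening records. It needs no extra patients, no new procedures and no change to the stated sample-size figures.

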### Demographic and practice information

Most residents of Olmsted County who are age 60 or older are female and white (>90%)[4]. While county residents are largely Northern European, the ERA index places this ethnicity as a high-risk population; thus, the potential sample may slightly over represent underserved minorities as a high-risk group.

The PCIM and FM have a combined population of about 21, 000 patients in this age group. The selection criteria of a score of 16 or greater on the ERA places these individuals in the upper decile of risk for hospitalizations, ED visits, nursing home placement, and death. The ERA is an electronically derived index number provided to all patients in the in PCIM and FM via the GDMS (Table 1).

#### Intervention - home telemonitoring

The Intel Health Guide is a U.S. Food and Drug Administration-approved device that is placed in the patient's home and connected to the health system via broadband Internet or 3G network. This device has video monitoring that allows real-time, face-to-face interaction with the provider team. Peripheral devices can be attached to measure blood pressure and pulse, oxygen saturation via pulse oximetry, glucose level via glucometer, and weight. The device incorporates a programmable, patient condition-specific touch-screen questionnaire for daily progress reporting.

The initial data collected is downloaded to the Web-based Intel Health Suite for access by the provider group via the Internet from any PC-based computer. Each patient has an individualized protocol of daily assessment questions and biometric parameters with predetermined action thresholds that are developed, revised, and monitored by the care team. An overview of the health guidelines is provided in Table 2. An example of one such parameter is the daily measurement of weight for patients with heart failure. If the weight falls outside of preset minimum or maximum values, the Intel Health Suite highlights the abnormality for the monitoring provider group.

**Table 2 T2:** Intel Health Guide health guidelines (general)

Measurement	Normal range
Systolic blood pressure	<140 mm Hg

Diastolic blood pressure	<90 mm Hg

Pulse oximetry	>88%

Weight gain of 2 pounds/day	<2 pounds a day

Weight gain of 5 pounds/week	<5 pounds gain a week

Fasting blood sugar	80-120 mg/dL

Heart rate	60-100 beats/min.

The implementation and monitoring of the Intel Health Guide involves a team of individuals. GE Healthcare installs the system, and a clinical assistant educates the patient on how to use the Intel Health Guide and serves as a contact for questions on the device or peripherals. The protocols are determined and loaded into the device by a registered nurse (RN) and modified by a nurse practitioner (NP) overseeing the care. The patient's primary care physician oversees the overall medical care of the telemonitoring through input from the RN or NP. One RN oversees the 100 subjects on the study every day.

The system provides alerts and feedback if there is a worrisome response to a question or if vital signs are outside of preset limits. The RN communicates with the patient and seeks assistance from the subject's primary care provider or the overseeing NP for management issues. The NP or RN communicates with the patient via teleconferencing to facilitate appropriate actions, which may include limited advice, reset thresholds, timely provider outpatient visit, or ED evaluation. The use of qualified staff allows for diagnostic and treatment decisions for a wide variety of complex medical conditions that may not be amenable to protocol-based care. The participants are told to call 911 for emergencies because the Intel Health Guide is not a life-saving device.

#### Intervention - usual care

The usual care intervention includes appropriate primary care and specialty office practice visits, as required. It also includes home healthcare, post-hospital outpatient visits, a nurse-generated phone call progress report within 1 business day of hospital dismissal, and standard clinic phone triage during business hours. It also involves a 24-hour nurse triage line for questions. Patients are informed of the currently available options to patients, including the previously mentioned options, extended-hours care, and Mayo Clinic Express Care.

#### Data collection

Data will be collected by the research team and maintained electronically in the Mayo system, which is backed up daily. All paper questionnaires will be collected and entered into the electronic environment for analysis via data entry using a double-entry method. To ensure standardized processing, all investigators and study team members will be formally educated on the questionnaire and the examination instruments.

#### Data handling and security

All patient information from the Intel Health Guide will be sent to a central repository in Arizona. This information will be available to the telemonitoring clinical team. The Intel Health Guide is a secure system that complies with Health Insurance Portability and Accountability Act (HIPAA) patient safety regulations. It has a highly encrypted format in a remote database, and transmissions are secured via the communication protocol Secure Sockets Layer.

